### Participant timeline, procedures, and follow-up

Pregnant women in the second and third trimesters fulfilling the inclusion criteria will be randomized to one of the following groups:

#### Intervention group

Prior to each IPTp-SP dose administration, a blood sample will be collected for malaria infection screening using US-RDT and microscopy, Hb measurement, and filter paper confection for parasite genotyping. The date of the next IPTp-SP administration will be planned accordingly and the sequences repeated until delivery. Pregnant women with a positive US-RDT will be treated with a full course of DHA-PQ over 3 days. The first dose will be administered under direct observation during ANC and the subsequent doses of the intervention on days 2 and 3 will be taken unsupervised at home. The treatment observance will be assessed by the field worker at the end of the treatment. In addition, a questionnaire on health and socio-demographic characteristics will be administered as well as a physical examination. A phone call as a reminder will be made 1 week prior to the scheduled date for the second dose of IPTp-SP. If the participant is not reachable, the field worker will visit the household in order to remind the visit date. The objective is to increase the number of IPTp-SP doses per woman.

#### Control group

In case of signs and symptoms suggestive of malaria infection, the nurse will follow the NMCP recommendations. An HRP-2 RDT will be performed and the participant treated with a full course of AL if positive. The first dose will be administered under direct observation at the ANC clinic, and the subsequent doses on days 2 and 3 will be taken unsupervised at home. Before treatment and regardless of the RDT result, the nurse will systematically collect a blood sample for hemoglobin measurement, microscopy, and filter paper for subsequent genotyping. Blood slides will be read after and treatment will be based on the result of RDTs as recommended by the NMCP in peripheral centers. In addition, a questionnaire on health and socio-demographic characteristics will be administered as well as a physical examination. No reminder will be used for the next ANC visit/IPT-SP dose date.

### Follow-up

#### Intervention group

One month after the first ANC visit with the first IPT-SP dose administration, the participant will be invited to the health facility for screened for malaria infection using the US-RDT. From that and at monthly intervals up to the last week of gestation, the pregnant women will be encouraged to visit the ANC clinic where the study nurse will perform a systematic screening using US-RDT and treatment with a full course of DHA-PQ if positive. The first dose will be administered under direct observation during ANC and the subsequent doses on days 2 and 3 will be taken unsupervised at home. The assessment of the treatment observance will be checked by the field worker at the end of the treatment. Before treatment and regardless of the US-RDT result during scheduled and unscheduled visits, the nurse will systematically collect a blood sample for hemoglobin measurement, microscopy, and filter paper for subsequent genotyping.

#### Control group

After the first IPT-SP dose administration, the date of the second one will be scheduled. No additional screening will be performed in this group. In case of signs and symptoms suggestive of malaria infection, the nurse will follow the NMCP recommendations. An HRP-2 RDT will then be performed and the participant treated with a full course of AL if positive. The first dose will be administered under direct observation during ANC and the subsequent doses on days 2 and 3 will be taken unsupervised at home. Before treatment and regardless of the RDT result during scheduled and unscheduled visits, the nurse will systematically collect a blood sample for hemoglobin measurement, microscopy, and filter paper spot for subsequent genotyping.

Irrespective of the study group, field workers will visit the treated participant on day 3 (final day of treatment) in order to assess uptake and compliance to treatment by administering a short questionnaire to check the empty packaging of the treatment. If the woman is severely ill at the time of the visit (e.g., from malaria or other causes and/or from complications from the pregnancy), they will be referred to the health facility for further care. In order to minimize the non-response in group 2, we will collect a blood sample (microscopy and blood spots) in all pregnant women regardless of the study group at fixed schedule visits: day 60 and day 80.

### Final study visit

The follow-up will end at the time of delivery. All study participants will be encouraged to deliver at the health facility that provides obstetric care. Mobile phone numbers will be obtained from each study participant as a means of communication. Women will be encouraged to call the field worker as soon as they enter labor in case of transport issues. In this case, the field worker will organize transport to the study health facility for obstetric care. A blood sample will be collected just before delivery for the detection of peripheral malaria infection (blood slide and blood spot on filter paper) and hemoglobin measurement. In addition, a placenta biopsy will be collected at delivery. The nurses will examine and weigh all newborns in order to measure one of the clinical outcomes. The same information will be collected as much as possible for those not delivering at the health facilities. The date of birth and date of examination and the date of data collection will be recorded. Figure 1.

**Fig. 1 Fig1:**
[figure not shown]
Schematic of study design

### Data collection and management

All data capture and management will be standardized across the study sites and considered privileged and confidential. The study participant will be attributed a unique identity number (ID). Once a unique number has been assigned, the nurse will match this number to their records. They will also keep a record of all eligible pregnant women in each village and update their status within the trial on a regular basis, e.g., keep note of ANC attendance, RDTs, and treatment visits, whether delivered and left the study or not, etc. All data will be double entered using OpenClinica® databases at each site. Consistency checks will be performed, and any outliers and missing data points will be checked against the original forms and subsequently amended in the dataset. Efforts will be made to minimize the amount of missing data in the trial, and whenever possible, information on the reason for missing data obtained. No adjustments will be made for missing outcome data, but missing data may be imputed for covariates.

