### Randomization and blinding

Eligible pregnant women will be randomly assigned (1:1) to either an intervention or control group computer-generated randomization schedule. Allocation concealment will be achieved by the use of sealed, opaque, and sequentially numbered envelopes each containing the study number and assignment of the participant to the study group. These envelopes will be prepared by an independent pharmacist based on the block randomization list generated by the study statistician. Once the participant has met all the eligibility criteria, the study clinician/nurse will open the envelopes to determine the group assignment and the study number of the participant. Recruitment will be “competitive” between the sites in the trial. Participants will be recruited over a 12-month period and followed for 6 months until delivery. To minimize cross-contamination, study subjects will be encouraged to attend the health facility within their catchment and not seek ANC or delivery elsewhere. It will not be possible to blind this intervention as pregnant women will quickly identify into which group they have been randomized into. Observer bias will be reduced where feasible. Blood films and placenta biopsies will be read by microscopists blinded to the identity and intervention status of the subjects.

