### Sample size considerations

We have assumed that this intervention will decrease placental malaria from 40 to 25%, with 80% power and at the 5% significance level, 152 pregnant women per group will be needed. With 10% of lost to follow-up, 170 pregnant women will be needed per arm.

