### Statistical methods

The randomization will ensure a balanced distribution of baseline characteristics between the two groups. A descriptive methodology will be used to analyze feasibility outcomes. Variables such as completion of the study participants recruitment within 12 months, the percentage of refusals, perception, and acceptability will be summarized per group. The primary clinical outcome will compare the prevalence of placental malaria (defined as the number of positive samples by the total number of samples) in each group and will be examined with logistic regression. This will be adjusted by gravidity, parity, season, and number of DHA-PQ. Appropriate statistical methods will be used to account for the influence of potential confounders (number of SP doses, number of co-morbidities, co-medication, the season of malaria transmission, gravidity, etc).

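### The protocol rules out any adjustment for missing placental outcomes, although antenatal contact differs by arm in an open trial, so the robustness of the primary comparison cannot be shown

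*Protocol article*

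**What the plan says.** Statistical methods gives the primary prevalence as a proportion of samples, "defined as the number of positive samples by the total number of samples", compared between groups by logistic regression. Data collection and management sets the rule for gaps: "No adjustments will be made for missing outcome data, but missing data may be imputed for covariates". Final study visit covers women who give birth elsewhere: "The same information will be collected as much as possible for those not delivering at the health facilities".

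On blinding, Randomization and blinding states that "It will not be possible to blind this intervention"; only the slide and biopsy readers are masked.

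Contact during pregnancy is set by arm:
- **Intervention:** a reminder call one week before the second IPTp-SP visit, a household visit if the woman cannot be reached, and encouraged monthly screening visits until the last week of gestation.
- **Control:** no reminder and no additional screening.
- **Both arms:** a field-worker visit on day 3 of any treatment, and blood sampling at days 60 and 80. The Follow-up section says this fixed sampling is meant to limit non-response in what it calls group 2, by context the control group.

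Sample size considerations assumes that "this intervention will decrease placental malaria from 40 to 25" per cent, and adds: "With 10% of lost to follow-up, 170 pregnant women will be needed per arm".

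**The concern.** Inflating the sample for losses restores the number of women analysed. It does not restore comparability if the women without a placenta differ between arms. Here one arm has more antenatal contact by design, and antenatal attendance is plausibly related both to infection and to whether a placenta is obtained. The blood samples at days 60 and 80 help describe infection during follow-up but do not replace a placental result.

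The rule permits imputation for covariates and excludes adjustment for the outcome, which is where selection would act. It is an affirmative statement and not a silence left to a statistical analysis plan: a plan that added imputation or weighting of the outcome would contradict the protocol. At stake is a comparison powered at 80%, whose result the Discussion says will demonstrate the impact on placental malaria. As written, nothing would show whether that result survives reasonable assumptions about the missing women.

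**Working it through.** **Inputs from the protocol.** 40% versus 25%, 80% power, 5% significance, 152 per group, 10% loss, 170 per arm (Sample size considerations). Loss below 10% is called acceptable (Primary feasibility outcomes). Missingness by arm and prevalence among missing women are not given; the values below are assumptions.

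**1. The plan's own figure.** Two-sided, pooled variance, mean prevalence 0.325:

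n = [1.960 × √(2 × 0.325 × 0.675) + 0.842 × √(0.40 × 0.60 + 0.25 × 0.75)]² / 0.15² = 151.9, so 152.

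With losses, 152 / 0.9 = 168.9, so 169 against the stated 170. The sample size is not in question. After 10% loss, 170 × 0.9 = 153 per arm remain and 17 are missing.

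**2. Bounds over all randomised women.** With a fraction m missing in each arm:

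- Lowest difference = (1 − m) × 0.40 − [(1 − m) × 0.25 + m]
- Highest difference = [(1 − m) × 0.40 + m] − (1 − m) × 0.25

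| m | Lowest | Highest |
|---|---|---|
| 10% | 0.360 − 0.325 = 3.5 points | 0.460 − 0.225 = 23.5 points |
| 15% | 0.340 − 0.3625 = −2.2 points | 0.490 − 0.2125 = 27.7 points |

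**3. Significance when the 17 missing women per arm are filled in.** Pooled z-tests, starting from 61/153 versus 38/153:

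| Assumed prevalence among missing (control / intervention) | Control | Intervention | z | p |
|---|---|---|---|---|
| Available samples only | 61/153 = 39.9% | 38/153 = 24.8% | 2.81 | 0.005 |
| 40% / 60% | 67.8/170 = 39.9% | 48.2/170 = 28.4% | 2.24 | 0.025 |
| 20% / 50% | 64.4/170 = 37.9% | 46.5/170 = 27.4% | 2.07 | 0.038 |
| 40% / 80% | 67.8/170 = 39.9% | 51.6/170 = 30.4% | 1.84 | 0.066 |
| 0% / 100% (worst case) | 61/170 = 35.9% | 55/170 = 32.4% | 0.69 | 0.49 |

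With missing controls at 40%, p passes 0.05 when prevalence among the missing intervention women reaches about 74%.

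**4. Direction.** Suppose no true effect (p = 40% in both arms), with m = 15% of controls and 5% of intervention women missing, and prevalence r among the missing. Available-sample prevalence is (p − m × r) / (1 − m).

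- r = 20%: control (0.40 − 0.03) / 0.85 = 43.5%; intervention (0.40 − 0.01) / 0.95 = 41.1%. Apparent benefit 2.5 points.
- r = 60%: control (0.40 − 0.09) / 0.85 = 36.5%; intervention (0.40 − 0.03) / 0.95 = 38.9%. Apparent harm 2.5 points.

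With a true 40% versus 25%, the same 15% / 5% split, and missing women at k times the prevalence of sampled women, sampled prevalence is p / [(1 − m) + m × k]. For k = 1.5 this is 37.2% versus 24.4%, a difference of 12.8 points with power 68%. For k = 2 it is 34.8% versus 23.8%, a difference of 11.0 points with power 56%. Equal 10% loss with k = 1 leaves 15 points and 80% power.

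**The case against.** Available-sample logistic regression is a recognised primary analysis for a binary outcome. It is valid for the arm effect if missingness depends only on arm and on modelled covariates, and gravidity, parity and season are in the model. The trial is a pilot, imputation details normally belong in the analysis plan, and the rule does not mention sensitivity analyses. Monitoring of missing data, a target below 1% missing values, and recording of reasons where possible are already planned. These points stand as reasons to keep the primary analysis. They do not remove a written rule against adjusting the outcome.

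Three stronger readings are tempting and the protocol does not support them.

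- **That the package changes who delivers at the facility.** Willingness to deliver there and to give a placental biopsy is an inclusion criterion for everyone. Encouragement and transport for delivery are the same in both arms, and reminders concern antenatal visits. An effect on placental sampling is a possibility only. Nor is all home contact confined to the intervention arm, given the day-3 visits.
- **That useful data go unused.** SP doses are a named adjustment factor, and all parasitological data enter the parasitological analyses. They are simply not assigned to the problem of missing placentas. PCR at days 60 and 80 is not stated; microscopy and blood spots are.
- **That the result is biased in favour of the intervention.** If missing women are poor attenders at higher risk and more numerous among controls, the bias runs against it. The 2.5-point shift is also less than half the standard error of the difference, √(0.435 × 0.565 / 144.5 + 0.411 × 0.589 / 161.5) = 5.7 points.

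**Conclusion.** The point holds in a limited form. The denominator is samples obtained, outcome adjustment is ruled out in writing, and part of the contact schedule is specific to one arm of an open trial. Missing placentas may therefore differ by arm and relate to infection, with direction and size unknown.

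At the planned 10% loss the data alone place a 15-point difference between 3.5 and 23.5 points over all randomised women; at 15% loss the range includes zero. Moderate assumptions leave the result significant (p about 0.04 at 20% / 50%). Losing significance needs strongly opposed assumptions, such as about 74% among missing intervention women against 40% among missing controls. All missingness splits and prevalences among missing women are assumptions; only the 10% and the 40% versus 25% come from the protocol. The change is worth making because it is cheap and is the only way to show whether the comparison is robust. It is not evidence that the trial will mislead.

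**What to change.** Keep the available-sample logistic regression as the primary analysis. Replace the sentence that excludes adjustment for missing outcomes with a pre-specified sensitivity analysis of all randomised women:

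1. Multiple imputation of placental status within group, from data already collected: gravidity, season, site, enrolment and day 60/80 infection results, and peripheral infection at delivery where available. Use infection measures taken in the same way in both arms, such as microscopy.
2. A tipping-point or best/worst-case table for the prevalence among missing women, varied separately by arm.
3. Missing placental samples reported by arm, with reasons.

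This needs no new data, visits or change to care. The cost is some wording, a little extra analysis, and possibly a less favourable statement about robustness.

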### Sample size considerations

We have assumed that this intervention will decrease placental malaria from 40 to 25%, with 80% power and at the 5% significance level, 152 pregnant women per group will be needed. With 10% of lost to follow-up, 170 pregnant women will be needed per arm.

### Statistical methods

The randomization will ensure a balanced distribution of baseline characteristics between the two groups. A descriptive methodology will be used to analyze feasibility outcomes. Variables such as completion of the study participants recruitment within 12 months, the percentage of refusals, perception, and acceptability will be summarized per group. The primary clinical outcome will compare the prevalence of placental malaria (defined as the number of positive samples by the total number of samples) in each group and will be examined with logistic regression. This will be adjusted by gravidity, parity, season, and number of DHA-PQ. Appropriate statistical methods will be used to account for the influence of potential confounders (number of SP doses, number of co-morbidities, co-medication, the season of malaria transmission, gravidity, etc).

The secondary clinical outcomes are pilot endpoints to include incidence rates (mean hemoglobin and birth weight), molecular and parasitological endpoints, safety, determinants of poor coverage of IPTP-SP, vector control effectiveness, and adverse events. Adverse events and serious adverse events will be monitored, managed, and recorded during the study. All study participants who receive at least one dose of the study drug will be included in the safety analysis. They will be recorded and tabulated for each treatment group. All parasitological data will be included in the parasitological analyses. For the evaluation of placental malaria and low birth weight in newborns, logistic regression will be performed while for the evaluation of the occurrence of malaria cases in pregnant women during the follow-up, Poisson regression will be implemented. The stratification or adjustment factors will be among others: the number of doses of IPTg-SP, the season of malaria transmission, and the gravidity. A statistical model will be used for the phone reminder by adjusting the number of calls (0, 1, 2) that the woman in the intervention group received before coming to this ANC. In this model, the number of calls for women in the control group will be 0. For the qualitative study, the acceptability will be assessed through focus group discussion and in-depth interviews. Topics covered by the in-depth interviews will comprise many components such as experience and opinions of the trial intervention groups, perceptions of the acceptability of the trial intervention, and implications for implementation. The interview guide will be used to collect data from pregnant women, health care workers, community health care workers, and traditional healers. The theoretical framework of acceptability developed by Mandeep Sekhon, Martin Cartwright, and Jill J. Francis will be used to assess acceptability. In this study, we will analyze the acceptability through the dimension of the burden, ethical consequences, experience, opportunity cost, intention, and affective attitude. The analysis will focus on the barriers and factors limiting adherence to IPTp-SP uptake.

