### Intervention description

In this study, 2 packages will be used as comparators: the standard of care package versus the new intervention package.

The current standard of care strategy for pregnant women attending ANC during the second and third trimester of pregnancy is based on three components (standard RDTs, AL, and scheduled visits without reminder).

The new intervention package will include three components (US-RDTs, DHA-PQ, and phone call reminders). Each of these three components has been shown to individually improve pregnancy outcomes. We hypothesize that a synergistic action of the three components will result in a higher impact on the outcomes of interest (placental malaria infection, low birth weight, and peripheral malaria infection at delivery) as compared to the current standard of care.

Comparisons will not be done between the individual components of each intervention package, but rather their combined effects between study groups: the intervention group (ultrasensitive malaria RDTs, DHA-PQ, and phone reminder) and the control group (the standard of care described above which includes standard RDT, AL, and scheduled visit without reminder).

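### The primary placental malaria model adjusts for DHA-PQ courses, and the plan also lists SP doses for adjustment; both arise after randomisation, so the group coefficient is not the package effect

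*Protocol article*

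**What the plan says.** All references are to the protocol article.

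- **Statistical methods, primary model.** Placental malaria prevalence is compared "in each group and will be examined with logistic regression". The next sentence fixes the covariates: "This will be adjusted by gravidity, parity, season, and number of DHA-PQ". I read the last item as the number of DHA-PQ courses a woman received.
- **Statistical methods, confounders.** The sentence after that promises suitable methods for "potential confounders (number of SP doses, number of co-morbidities, co-medication, the season of malaria transmission, gravidity, etc".
- **Statistical methods, further on.** After a sentence that names logistic regression for placental malaria and low birth weight and Poisson regression for malaria during follow-up, the plan adds: "The stratification or adjustment factors will be among others: the number of doses of IPTg-SP, the season of malaria transmission, and the gravidity".
- **Intervention description.** "The new intervention package will include three components (US-RDTs, DHA-PQ, and phone call reminders". The same section says that the comparison is of the combined effects of the two packages, not of their components.
- **Intervention group.** A positive ultrasensitive test leads to a DHA-PQ course. Of the reminder it says: "The objective is to increase the number of IPTp-SP doses per woman".
- **Control group.** For women with suggestive signs or symptoms: "An HRP-2 RDT will be performed and the participant treated with a full course of AL if positive".

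No unadjusted or baseline-covariate-only model is named as primary.

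**The concern.** Adjustment in a randomised trial should use variables fixed before allocation. The number of DHA-PQ courses is not one of them. It is a component of the treatment being tested, it is triggered by a positive test after allocation, and the control arm is assigned a different drug. Within the intervention arm it mixes two things: how prone a woman is to infection, and how much of the study treatment she received. The number of SP doses is a target of the reminder, so it lies on the path from the intervention to the outcome.

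Holding either fixed changes the question. Placental malaria is the primary clinical outcome and the basis of the sample size. The Discussion section expects the pilot to demonstrate the impact on it and to inform larger-scale use. A benefit that the model created, or one that it removed, would misinform that step.

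**Working it through.** **1. The plan's own sample size.** Inputs (Sample size considerations): 40% versus 25%, 80% power, 5% level, taken as two-sided. With mean proportion 0.325:

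n = [1.960 × √(2 × 0.325 × 0.675) + 0.842 × √(0.40 × 0.60 + 0.25 × 0.75)]² / 0.15² = (1.298 + 0.550)² / 0.0225 ≈ 152 per group.

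This reproduces the stated 152. Then 152 / 0.90 = 169, against the stated 170. The power at 152 is 80.0%. The contrast powered is the plain two-group one, with odds ratio (0.25/0.75) / (0.40/0.60) = 0.50.

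**2. What the stated model estimates.** Leaving out the baseline terms:

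logit P(placental malaria) = a + b × group + c × courses.

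In controls, courses = 0 by design, so c is learned only from the intervention arm. The coefficient b is then the model-based log-odds difference between an intervention woman with zero courses and the control arm. Zero courses means mostly women who never tested positive, together with any who missed screening. That is a selected subgroup set against a whole randomised arm.

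**3. Size.** The protocol gives no infection frequency, spread of risk between women or SP effect, so every input below is an assumption. Simulations used 152 per arm, 40% control prevalence and 2,000 runs per scenario. Odds ratios are the exponentiated median group coefficient.

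*(a) No true effect.* A woman's infection risk raises both her course count (Poisson, capped at 5) and her odds of placental malaria.

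| SD of risk (log-odds) | Mean courses | OR, group only | OR, adjusted for courses | Type I error, group only | Type I error, adjusted |
|---|---|---|---|---|---|
| 0 | 0.5 | 1.00 | 1.00 | 4.6% | 4.5% |
| 0 | 1.0 | 1.00 | 1.00 | 4.4% | 4.3% |
| 0 | 1.5 | 1.00 | 1.00 | 5.3% | 5.1% |
| 0.5 | 0.5 | 1.00 | 0.91 | 5.3% | 6.6% |
| 0.5 | 1.0 | 1.00 | 0.82 | 5.5% | 9.6% |
| 0.5 | 1.5 | 1.00 | 0.77 | 4.3% | 14.2% |
| 1.0 | 0.5 | 1.00 | 0.75 | 4.8% | 18.6% |
| 1.0 | 1.0 | 1.00 | 0.65 | 5.1% | 36.3% |
| 1.0 | 1.5 | 1.00 | 0.56 | 5.7% | 50.7% |

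Where risk varies, nearly all rejections under adjustment favour the intervention.

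*(b) Benefit delivered by the courses.* No spread of risk, mean 1.0 course, log-odds effect per course as shown. Power is the rate of significant results in favour of the intervention.

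| Effect per course | Intervention prevalence | OR, group only | Power | OR, adjusted for courses | Power |
|---|---|---|---|---|---|
| −0.7 | 26.9% | 0.55 | 69% | 0.99 | 2% |
| −0.8 | 25.8% | 0.52 | 75% | 1.02 | 2% |
| −0.9 | 24.6% | 0.49 | 80% | 1.01 | 3% |

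*(c) Benefit partly or wholly through SP doses.* The reminder is assumed to raise the mean from 2.2 to 3.2 doses. Results are for risk SD 0.5 and 1.0.

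| Share through SP | OR, group only | Rejection rate | OR, adjusted for SP doses | Rejection rate |
|---|---|---|---|---|
| None | 0.50 and 0.50 | 79% and 80% | 0.50 and 0.50 | 69% and 70% |
| Half | 0.51 and 0.52 | 78% and 78% | 0.70 and 0.71 | 24% and 22% |
| All | 0.54 and 0.53 | 72% and 72% | 1.00 and 0.99 | 5% and 5% |

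Even when SP carries none of the benefit, adjusting for it costs about 10 percentage points of power, because dose count and group are correlated.

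**The case against.** The strongest points on the other side are these.

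- **Direction.** A reader might infer from (a) that adjusting for DHA-PQ always favours the intervention. The documents do not support that. Table (b) shows a real benefit erased, and with no spread of infection risk a null effect stays unbiased. Since DHA-PQ is meant to be effective, both mechanisms may act together, and the net direction cannot be determined from the protocol. This objection stands.
- **SP doses.** Only the DHA-PQ count is in the sentence that fixes the primary covariates. SP doses come in the next sentence, under unspecified methods for confounders, and again in a paragraph that opens with secondary outcomes. That paragraph does name placental malaria, so SP adjustment of the primary analysis is a reasonable reading, but it is less certain than the DHA-PQ adjustment.
- **Co-medication.** A reader might count this as post-randomisation too. The protocol does not say when it is recorded. If recorded at enrolment, it is a legitimate covariate.
- **Zero in controls.** The Study setting section says either AL or DHA-PQ is recommended in the second and third trimesters, so a control woman could receive DHA-PQ outside the study plan. That would not make the count a baseline variable.
- **Pilot status.** The feasibility outcomes are analysed descriptively and are unaffected, and prevalence by group would presumably be visible. This limits the harm. It does not remove it, because the trial is sized on placental malaria and the stated model is the one that would test it.

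Nothing elsewhere in the article corrects the covariate list. An analysis plan that is not shown cannot be assumed to do so, because the covariate is named here.

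**Conclusion.** The covariate choice is wrong as written. The primary model conditions on a component of the randomised treatment, and the surrounding text invites conditioning on a second variable that the intervention is designed to change. The group coefficient is then neither the combined package effect set as the comparison in Intervention description nor the 40% versus 25% contrast that was powered.

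That conclusion rests on the text alone. The sizes do not: they depend on assumed infection frequency, spread of risk, course effect and SP effect, and serve only to show that the distortion can be large. Under the assumptions used, adjusting for DHA-PQ count could produce a type I error of about 7% to 51%, or could reduce power of 69% to 80% to 2% to 3%. Adjusting for SP doses removes whatever part of the benefit works through them.

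A reader might also infer that the sample size is at fault. It is not: 152 per group is correct for the unadjusted comparison. Gravidity and parity are sound covariates, and so is season if taken at enrolment.

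**What to change.** - Define the primary model as placental malaria on group as randomised plus baseline covariates only: gravidity or parity, and season at enrolment.
- Remove the number of DHA-PQ courses and the number of SP doses from the primary and secondary effect models. Remove co-medication as well, unless it is recorded at enrolment.
- Report DHA-PQ courses and SP doses by group as process measures. Label any analysis of how the effect is mediated as exploratory.

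The cost is a change of wording in Statistical methods, best made before the outcome data are analysed. No new data are needed, and the sample size of 152 evaluable women per group does not change.
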